## Procedure for participants who drops out or in other way interrupts the trial

Participants have the right to withdraw from the trial at any given time and for whatever reason in accordance with the Declaration of Helsinki. Sponsor and investigator also have the right to withdraw a participant at any given time.

The reason for withdrawal will be stated in the participants Case Report Form.

## METHODOLOGY

### General treatment plan and medical dosing

### Trial schedule for the participants:

Does Perineural Clonidine Prolong the Duration of an Adductor Canal Block When Controlling for Possible Systemic Effects?  
- A Randomized Paired Trial in Healthy Volunteers  
SM1-JH-14, EudraCT 2014-005640-18, VEK nr SJ-437

- Information about the project is given by the principal investigator. Time for questions and consideration will be provided.
- The principal investigator [name] (MD) or sub investigator (MD) obtains a short medical history according to the Case Report Form going through in- and exclusion criteria. Height, weight Blood pressure and Pulse are measured.
- All sensory and motor modalities are tested on the participants to familiarize them with the procedures.
  - Temperature-discrimination test with an alcohol swab
  - Pin-prick test
  - Pain during tonic heat stimulation (baseline value is measured)
  - Warmth detection threshold (WDT)
  - Heat pain detection threshold

Baseline measurements are done for all modalities.

- **Ultrasound guided ACB:**

- The ACB is performed using ultrasound guidance as a single injection of local anesthetics next to the saphenous nerve in the adductor canal at a mid-thigh level.
- The ACB's are performed on the RIGHT side first followed immediately by the opposite treatment on the LEFT side according to randomization.
- All participants receive both treatments, one in each leg.

- **Trial medication:**

- **Treatment A:** ACB with 20 ml ropivacaine 0,5 % + 1,0 ml clonidine 150 µg/ml
- 
- **Treatment B:** ACB with 20 ml ropivacaine 0,5 % + 1,0 ml isotonic saline
- **No other medication is planned during the trial period.**
- Time of block performance (removal of needle) in the right arm is registered as T=0.
- The participants are monitored with continuous ECG, pulse oximetry and blood pressure every 15 minutes for 4 hours after administration of the trial medication.
- Sedation is measured every hour post block using a verbal rating scale (VRS) from 0-3 (0 no sedation, 1 light sedation, 2 moderate sedation, 3 pronounced sedation).
- Temperature discrimination test with an alcohol swab, pin-prick and tonic heatstimulation is performed at T=1h and 4h post block. If temperature discrimination is retained at t = 1h the sensory tests are also done at t = 2h and t = 3h. From 4 h

Does Perineural Clonidine Prolong the Duration of an Adductor Canal Block When Controlling for Possible Systemic Effects?  
- A Randomized Paired Trial in Healthy Volunteers  
SM1-JH-14, EudraCT 2014-005640-18, VEK nr SJ-437

and forth the tests are done every hour until values are normalized/returned to baseline. If necessary after the first 4 hours there will be given opportunity to sleep and sensory tests as well as blood pressure measurements (if subjects have stabile blood pressure) is omitted here.

- WDT and HPDT are performed at T=1h. If pain score during tonic heat stimulation equals 0 WDT and HPDT are omitted. When pain score during tonic heat stimulation again is > 0, WDT and HPDT are performed every hour until the values have normalized.
- Similarly, temperature discrimination testing with an alcohol swab is performed every half hour if the pain score during tonic heat stimulation is > 0.
- The individual test finishes when the value has returned to baseline.
- A participant is defined as a non-responder and withdrawn from the trial if normal temperature discrimination and pin-prick persists in one or both legs 2h after block performance.
- A block is defined as partial if there is a reduced sensitivity to cold (alcohol swab) and pin-prick, but VAS > 0 tonic heat stimulation at t = 2h.
- Side effects from t=0 until discharge is recorded in the CRF.
- When all values are normalized the trial is terminated and the participant sent home.

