## Outcomes

### Primary outcome measure

- The difference in duration of sensory block between ACB with ropivacaine + clonidine versus ACB with ropivacaine + placebo, measured as time from block performance (removal of the needle) until an alcohol swab feels cold again (temperature discrimination).

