- **Determination of heat-pain threshold (HPDT)** represents the lowest temperature perceived as painful. Start temperature for the thermode is 32 ° C. The temperature rises by 1 ° C/sec during the threshold determination and 5 ° C/sec at the return to the starting temperature after the test. The participant is asked to press a button, when the thermode feels painful while also finishing heat stimulation. If the limit of temperature increase beyond 52 ° C before recording a threshold value the thermode automatically returns to its starting temperature and 52 ° C is recorded. Each threshold value is calculated as the average of four stimulations; stimulations are presented 6-10 seconds apart. The duration of sensory block assessed by HPDT, defined as the time from block performance until HPDT is normalized.

The trial lasts from the introduction until the nerve block wears off (typically 10-14 hours). The participants will receive the above-mentioned treatments according to a computer-generated randomization list.

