## STATISTICAL ANALYSIS

### Sample size calculation

Does Perineural Clonidine Prolong the Duration of an Adductor Canal Block When  
Controlling for Possible Systemic Effects?  
- A Randomized Paired Trial in Healthy Volunteers  
SM1-JH-14, EudraCT 2014-005640-18, VEK nr SJ-437

A few studies have compared the duration of perineural clonidine with systemic clonidine, but these studies have examined combination with bupivacaine(4, 21), mepivacaine(3) and levobupivacaine(22) and not perineural ropivacaine. El Saied (9) investigated ropivacaine with clonidine as an adjuvant perineurally vs. ropivacaine alone in a study with 50 patients. The addition of clonidine as an adjuvant prolonged the sensory blockade 489-628 minutes (95% CI 90-187). In a yet unpublished study by our group on healthy volunteers, we found a sensory duration of an ACB with 20ml ropivacaine 5 mg/ml of 22 (SD 4) hours. Accordingly, we find that a 240 minutes prolongation of block duration will be clinically relevant. With a type 1 error risk of 5% and a type 2 error risk of 10% and an SD of 240 minutes, a total of 18 subjects is needed in this paired trial to show a difference of 240 minutes. In order to compensate for possible dropouts, we plan to include 21 participants.

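### The primary swab test may be skipped during a sleep period of unlimited length, so recoveries in that period are dated too late and the estimated prolongation can be shrunk or inflated

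*Protocol*

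**What the plan says.** The primary outcome is the between-leg difference in block duration, "measured as time from block performance (removal of the needle) until an alcohol swab feels cold again (temperature discrimination". The Sensory tests section defines duration in the same way.

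Under Trial schedule for the participants, testing from 4 h onward is hourly: "and forth the tests are done every hour until values are normalized/returned to baseline". The swab becomes more frequent once heat pain returns: "temperature discrimination testing with an alcohol swab is performed every half hour if the pain score during tonic heat stimulation is > 0". The schedule then makes an exception: "If necessary after the first 4 hours there will be given opportunity to sleep and sensory tests as well as blood pressure measurements". The sentence ends by dropping these assessments while the participant sleeps. The swab is not exempted. The protocol states no block start time, no sleep hours, no maximum gap and no rule for dating a recovery that happens during sleep.

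The protocol gives two expected durations. The sample size section says "we found a sensory duration of an ACB with 20ml ropivacaine 5 mg/ml of 22 (SD 4) hours". The end of the Sensory tests section says "until the nerve block wears off (typically 10-14 hours". Data handling sends the durations to a paired t-test, or to a Wilcoxon signed-rank test if they are not normal.

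**The concern.** A block expected to last about 22 h, with 4 h more hoped for on the clonidine side, runs through a night for any ordinary daytime start. The untested period can therefore fall where recovery is expected. A leg that recovers during sleep can be recorded only at the first test after waking, up to a whole sleep period late. Half-hourly swabbing while awake does not help with this.

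Both legs of a participant share the same gap, but with a real treatment effect they do not meet it equally. If mainly the shorter-lasting legs recover overnight, they are lengthened and the difference shrinks. If mainly the longer-lasting legs do, the difference grows. What is at stake is the estimated prolongation, which the protocol judges against 240 min.

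**Working it through.** **The plan's own sample size.** For a paired design, n = ((z_α + z_β) × SD_diff / δ)², with δ = 240 min and 90% power.
- SD_diff = 240, two-sided 5%: (1.960 + 1.282)² = 10.5, so 11 (13 with the t distribution).
- SD_diff = 240√2 (per-leg SD, uncorrelated legs), one-sided 5%: 2 × (1.645 + 1.282)² = 17.1, so 18.

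The stated 18 is reached only on the second reading. That is a separate matter, and the present point does not rest on it.

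**Inputs from the protocol.** Placebo leg mean 22 h, SD 4 h; true difference 240 min, so clonidine leg mean 26 h; hourly tests.

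**Assumed, because not in the protocol.** Normal durations; SD 4 h in both legs; sleep 23:00-07:00, with the last test at 22:00 and the next at 07:00; between-leg correlation 0 or 0.5. The recorded time R(T) is the first test actually done at or after the true recovery time T.

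**Share of legs recovering during sleep.** For an 08:00 start, sleep covers 15 to 23 h after the block.
- Placebo: Φ((23−22)/4) − Φ((15−22)/4) = Φ(0.25) − Φ(−1.75) = 0.599 − 0.040 = 56%.
- Clonidine: Φ(−0.75) − Φ(−2.75) = 0.227 − 0.003 = 22%.

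For a 17:00 start the first night covers 6 to 14 h and catches few legs. The second night covers 30 to 38 h.
- Clonidine: Φ(3) − Φ(1) = 0.999 − 0.841 = 16%.
- Placebo: 1 − Φ(2) = 2%.

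So early starts mainly delay placebo legs, and late starts mainly delay clonidine legs.

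**Mean recorded difference, E[R(T_clonidine) − R(T_placebo)], by simulation, true value 240 min:**

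| Block start | First-night sleep, h after block | Placebo legs in it | Recorded mean | Error |
|---|---|---|---|---|
| 08:00 | 15-23 | 56% | 168 min | −72 |
| 10:00 | 13-21 | 39% | 198 min | −42 |
| 14:00 | 9-17 | about 10% | 256 min | +16 |
| 17:00 | 6-14 | 2% | 307 min | +67 |

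- The correlation hardly changes these means.
- Testing right up to 23:00 gives 174 min at 08:00, 199 at 10:00 and 245 at 14:00: the same pattern, slightly milder.
- A 6 h sleep period gives about 190 to 222 min for 08:00-10:00 starts.
- With hourly swabs continued overnight the mean is 240 min at every start, because hourly rounding cancels between legs.

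**Scale.** At 08:00 the error is 72/240 = 30% of the target difference. It is 72/139 = 52% of the prolongation that the sample size section takes from the earlier ropivacaine study (628 − 489 = 139 min).

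**The test.** With no true difference, the mean recorded difference is 0 and type I error is about 4-5%. At n = 18 (two-sided paired t-test, true 240 min), power changes as follows:
- Uncorrelated legs: about 81% with overnight testing; 74% for an 08:00 start; 77% for 10:00.
- Correlation 0.5: about 98%; 93%; 96%.

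**Interval-censored analysis.** In a check with n = 21, an 08:00 start, correlation 0.5 and 150 simulated trials, the exact-time mean was 169 min. A normal random-intercept model fitted to the intervals gave 240 min. The SD of the estimate was 41 and 56 min respectively.

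**The case against.** Sleep is allowed only if necessary, and the clock times are assumptions. At the 22 h mean the error passes from negative to positive as the start time moves later, and near 14:00 it is small. Letting volunteers sleep when they are observed for about a day is an open, practical choice. No dating rule is written, so using the waking time is an inference, and an analysis plan not seen here could treat the times as interval-censored. All of this stands. It limits what can be said about direction and size, but an analysis plan cannot recover tests that were never done, and the waking test is the only observation that meets the protocol's outcome definition.

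Several stronger readings are tempting but not supported:
- **That tied zeros invalidate the test.** Ties do occur: at an 08:00 start with correlation 0.5, both legs recover in the same sleep window in 16% of participants. Because the gap is shared, false-positive risk is not raised, so whether clonidine prolongs the block is still validly tested.
- **That the error equals the published effect.** At an 08:00 start it is about half of it, and at other starts less.
- **That the 10-14 h duration proves a far larger error.** It would put recovery after a morning block close to bedtime and reverse the direction of the error. The protocol gives no SD for that duration, so any figure for its size depends on the SD chosen.

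**Conclusion.** The point holds as a should-fix matter. Followed as written, the schedule can misstate the primary estimate materially: by up to about 70 min either way for a true 240 min, for starts between 08:00 and 17:00 with an 8 h sleep period. It can also be nearly harmless at a favourable start time. The protocol fixes none of the quantities that decide which applies, and its two stated durations imply opposite directions for a morning block. A reader might infer a known, systematic bias or an invalid trial; the documents show neither. What they show is an unbounded untested period, placed where the sample size section expects recovery, feeding analyses that take the recorded times as exact. The loss of power is secondary, at most about 7 percentage points at n = 18 for starts between 08:00 and 10:00.

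**What to change.** 1. In the trial schedule, exempt the swab test on both legs from the sleep omission, or state a maximum untested gap. The other sensory tests can still be skipped. Cost: brief wakings of participants who are already under observation.
2. For any recovery inside a gap, record the last test that was not cold and the first that was. Analyse these intervals with a paired interval-censored model, such as a normal model with a participant effect, at least as a sensitivity analysis beside the tests in Data handling. Cost: reliance on a distributional model and a clearly larger standard error (56 against 41 min in the check above, 56/41 = 1.37, or 37% more). The smaller figure belongs to an estimate centred on the wrong value.
3. Reconcile the 22 h and 10-14 h durations, then state a block start time that places expected recovery of both legs in tested hours as far as possible. Cost: a text correction and a scheduling constraint.

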## Participants completion and interruption of trial

- A participant has completed the trial, when the treatment plan has been followed until one hour after the alcohol-swab again is perceived as cold (normal temperature discrimination).
- A participant who interrupts the trial, is a participant who is included in the trial and has given written informed consent, but has not completed the trial, whether trial medication was given or not. If a participant does not complete the trial, or drops out, a follow-up plan must be stated on if and how data is collected.

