## Reasons for trial interruption

A participant can be withdrawn from the trial under the following circumstances:

- A participant is defined as non-responder and withdrawn from the trial if temperature discrimination is present, when stimulated with an alcohol swab in one or both legs 2 hours post block. The participant will be monitored for adverse events for 4 hours after block performance before discharge.
- If the investigator finds it best for the participant.
- If the participant wishes to interrupt the trial.

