## Does Perineural Clonidine Prolong the Duration of an Adductor Canal Block When Controlling for Possible Systemic Effects?

- A Randomized Paired Trial in Healthy Volunteers  
SM1-JH-14, EudraCT 2014-005640-18, VEK nr SJ-437

Participants Case Report Form. Should an adverse event occur more than 36 hours after administration of the trial medication, and no apparent association or connection to the trial medication can be made, it is not considered an adverse event.

Beginning and end, severity and symptoms related to the assumed adverse event following administration of the trial medication is noted. The severity of the adverse event and the association to the trial medication is evaluated according to the following guidelines by the investigator.

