### **Guidelines for adverse events and causal relations to treatment**

1. Not related – No temporal relation, other causes more likely.
2. Possibly related – Less clear connection, other causes may also be possible.
3. Probably related – Clear temporal connection with clinical improvement after termination of trial medication, and not reasonably explained by the participants known clinical condition.
4. Related – Clear temporal connection with retesting or clinical assessment.

Participants experiencing adverse events will be monitored with relevant clinical assessments and lab tests according to the treating doctor's decision. All adverse events will be followed until satisfactory restitution or stabilization.

A Serious Adverse Event = SAE is an event that leads to risk of death or handicap for the participant (or their offspring) including, but not limiting to, an event that result in:

- Death
- Life threatening circumstance. Participant was, assessed by the investigator, at apparent risk of death by the adverse event as it occurred.
- Hospital admission
- Permanent invalidation
- Innate anomaly

A product resume for clonidine chapter 4.8 and the product resume for Ropivacaine chapter 4.8 from the department of health homepage as a reference document, when assessing whether a serious adverse event is expected or unsuspected.

Reduced sensitivity and motor deficits are a known effect of nerve blocks and will not be reported to the authorities unless strength and sensitivity is not regained within 36 hours after nerve block. There is a known risk of falling when nerve blocks involves n. femoralis, accordingly falling is not seen as an adverse event unless injury occurs in relation to the fall. The risk of falling is probably lower in relation to adductor channel blocks, all possible precautions will be taken to avoid falls.

Bradycardia, hypotension, sedation and dizziness are also known side effects of clonidine and will not be considered an adverse event.

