## Reporting AEs and SAEs

Investigator is responsible for registration of any AEs and SAEs in the participants Case Report Form.

Sponsor is responsible for ongoing monitoring of the trials risk/benefit relations. If events occur that may jeopardize the safety of the participants or the trial, the competent authority should **always** be informed. Similar reporting should also be done to all investigators and ethical committees.

In addition, the following guidelines of reporting to authorities are followed. All events and side effects of the medication are to be reported.

Sponsor is ongoing informed by the investigator on adverse events. By the completion of the trial, the final report should include a description of all adverse events.

Serious Adverse Events – SAE are reported to the sponsor by the investigator immediately. SAE's are reported yearly to the ethics committee during the entire trial period along with a report on the safety of the participants.

Serious adverse reaction – SAR are reported by the sponsor (sponsor-investigator) yearly to the competent authority. The report also entails details on the safety of the participants.

Suspected unexpected serious adverse reaction – SUSAR are reported by the sponsor (sponsor-investigator) to the competent authority and the ethical committee within 24 hours. Report to the competent authority will be done using the electronic form for reporting SUSAR.

Deadly or life-threatening SUSAR's are reported within **7 days** after sponsor's awareness of the event. Within **8 days** of the report, the sponsor must inform the competent authority of all relevant information on the follow-up of the event.

All other unexpected or serious suspected events must be reported to the authorities within 15 days of the event.

Any report to the authorities must be accompanied by a statement on the consequences for the trial.

It is recommended that sponsor (sponsor-investigator) informs the manufacturer of the event.

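### Side-effect recording stops at discharge, and nothing is actively collected between discharge and the protocol's own 36-hour limits

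*Protocol*

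**What the plan says.** All references are to the Protocol.

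- **Recording period.** Trial schedule for the participants: "Side effects from t=0 until discharge is recorded in the CRF".
- **Discharge of completers.** Same section: "When all values are normalized the trial is terminated and the participant sent home". The section on completion and interruption defines a completer as followed "until one hour after the alcohol-swab again is perceived as cold (normal temperature discrimination").
- **Discharge of non-responders.** Reasons for trial interruption: "The participant will be monitored for adverse events for 4 hours after block performance before discharge". A participant is a non-responder if the block has failed in one leg or in both. The section on risks, by contrast, says participants stay under observation until the block has worn off.
- **36 h, first use.** The adverse event definition has an exclusion that begins "Should an adverse event occur more than 36 hours after administration of the trial medication". It applies only if there is also no apparent connection to the medication.
- **36 h, second use.** Guidelines for adverse events: reduced sensitivity and motor deficits "will not be reported to the authorities unless strength and sensitivity is not regained within 36 hours after nerve block".
- **Reporting.** Reporting AEs and SAEs: "By the completion of the trial, the final report should include a description of all adverse events".
- **Motor testing.** Trial schedule: "All sensory and motor modalities are tested on the participants to familiarize them with the procedures". The list beneath that sentence holds five tests, all sensory.

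**The concern.** The schedule fixes when recording stops, and the adverse event section fixes a later time up to which events matter. Nothing in the protocol connects the two. If the schedule is followed as written, the adverse event data end at a time that depends on how long each volunteer's block lasted, and for nearly everyone that is before 36 h. After that, an event reaches the case report form only if the volunteer chooses to report it.

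The final report is meant to describe all adverse events of a drug that, by the protocol's own account, is not approved for perineural use. The volunteers gain no direct benefit, and the protocol calls the risk minimal. Data cut off early, with no record of strength, are a weak basis for confirming or questioning that judgement.

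**Working it through.** The plan gives no figure for this gap, so there is none to reproduce. The gap follows from its stated times.

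**Inputs**
- Sensory duration with ropivacaine alone: 22 h, SD 4 h (Sample size calculation).
- Prolongation to be detected: 240 min = 4 h (same section).
- Time kept after cold sensation returns: 1 h (completion rule).
- Alternative typical duration: 10 to 14 h (end of Sensory tests).
- Non-responder discharge: 4 h (Reasons for trial interruption).
- Limit: 36 h.

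**Gap = 36 h − discharge time**

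| Case | Discharge | Gap | Share of 36 h |
|---|---|---|---|
| Ropivacaine-alone duration | 22 + 1 = 23 h | 13 h | 36% |
| With planned prolongation | 22 + 4 + 1 = 27 h | 9 h | 25% |
| 10 to 14 h as length of stay | 10 to 14 h | 22 to 26 h | 61 to 72% |
| 10 to 14 h as block duration, plus 1 h | 11 to 15 h | 21 to 25 h | 58 to 69% |
| Non-responder | 4 h | 32 h | 89% |

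Discharge waits for the slower leg. I took durations as bivariate normal with means 22 and 26 h and SD 4 h in each leg. Discharge is then the larger of the two plus 1 h. The protocol gives no between-leg correlation, so I assumed 0, 0.5 and 0.9. With 400,000 draws each:
- mean discharge is 27.8, 27.3 and 27.0 h;
- median gap is 8.3, 8.7 and 9.0 h.

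That gives about 8 to 13 h for completers on the sample size figures. The 13 h is the upper end, because it ignores the slower leg.

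**Share leaving before 36 h**
- Mean 23 h: Φ((36 − 23)/4) = Φ(3.25) = 0.999.
- Mean 27 h: Φ((36 − 27)/4) = Φ(2.25) = 0.988.
- Slower leg, simulated: 0.987 to 0.988.

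About 99% of completers are therefore discharged before the limit.

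**Which events are exposed**
- *Sensory deficit lasting past 36 h, completer:* seen, because he is not sent home until sensory values are normal.
- *Weakness:* not measured at baseline, before discharge or at 36 h. No strength test is described, and no motor value enters the discharge rule.
- *Later or recurrent symptoms, haematoma, injurious fall at home:* learned of only if volunteered. A fall with injury counts as an adverse event under the Guidelines.
- *Non-responder with one failed block:* the other leg may be blocked for an expected 22 h, yet monitoring is stated for 4 h only.

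**Rarity of the gravest event.** The protocol puts nerve injury at 0.04%. With 21 × 2 = 42 blocks, the chance of at least one is 1 − (1 − 0.0004)^42 = 1.7%. The likelier loss is of minor events.

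**The case against.** The best defence is that 36 h is an outer limit on attribution and not a collection period. Adverse events are defined as occurring during the trial, and the schedule says the trial ends for a participant when his values are normal. Recording until discharge would then agree with the definition. That reading is possible, but it leaves the 36 h exclusion almost without function, since about 99% of completers have left by then. It also does not say how anyone would know whether strength had returned by 36 h.

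Several stronger conclusions are tempting, and the documents do not support them.

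- *A reader might infer that events after discharge are always lost.* The adverse event section asks for all adverse events to be noted without naming discharge as a stop, and requires identified events to be followed to recovery or stability. A volunteered report could be recorded. The participant information is not shown, so whether volunteers are told to report later symptoms cannot be judged. What is missing from the protocol is a planned contact.
- *A reader might infer that the neurological rule has no data behind it.* For sensation in completers it does, because discharge waits for sensory recovery.
- *A reader might infer that systemic clonidine effects would be missed.* The Guidelines exclude bradycardia, hypotension, sedation and dizziness from adverse events, so a longer window would not add those four to the count.
- *A reader might infer bias between treatments.* Each volunteer receives both treatments and goes home once, so both legs share one end of recording.

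It is also fair to say that the block is described as almost purely sensory, that only minor motor block is expected, and that no outcome is motor. The missing strength test is therefore a matter of consistency and not a lost endpoint.

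**Conclusion.** The point holds as a conflict over the adverse event collection period. Recording ends at discharge, two rules run to 36 h, and no active collection is specified in between. The gap is about 8 to 13 h for completers on the sample size durations, about 21 to 26 h if 10 to 14 h is right, and 32 h for non-responders discharged at 4 h. The two stated durations disagree, and the size of the gap depends on which applies.

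The figures assume normal durations, SD 4 h in both legs, the correlations stated, and discharge 1 h after cold sensation returns in the slower leg. If another test normalises later, discharge is later and the gap shorter.

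The consequence is confined to the completeness of the safety data. The primary outcome and the comparison between legs are not affected. The change is worth making because it is cheap and uses a limit that the protocol already sets.

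**What to change.** 1. In the trial schedule, replace recording until discharge with recording of adverse events from t=0 until 36 h after block performance, so that it agrees with the adverse event section.
2. Add one scheduled telephone contact at or after 36 h for every participant who received trial medication, including those withdrawn. Ask by leg about sensation, strength, pain, haematoma and falls, and enter the answers in the case report form.
3. Reconcile the 4 h discharge of non-responders with the statement that participants are observed until the block has worn off. Which of the two applies is for the sponsor and investigator to decide.
4. Make the mention of motor modalities in the schedule, and of strength in the reporting rule, consistent with the tests actually listed, either by adding a recorded test or by changing the wording.

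The cost is 21 calls, a few lines in the case report form and a slightly higher adverse event count, because volunteers are now asked. No dose, treatment or efficacy endpoint changes.
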